## Abstract

**Background:**

Vascular ulcers are commonly seen in daily practice at all levels of care and have great impact at personal, professional and social levels with a high cost in terms of human and material resources. Given that the application of autologous platelet rich plasma has been shown to decrease healing times in various different studies in the hospital setting, we considered that it would be interesting to assess the efficacy and feasibility of this treatment in primary care. The objectives of this study are to assess the potential efficacy and safety of autologous platelet rich plasma for the treatment of venous ulcers compared to the conventional treatment (moist wound care) in primary care patients with chronic venous insufficiency (C, clinical class, E, aetiology, A, anatomy and P, pathophysiology classification C6).

**Design:**

We will conduct a phase III, open*-*label*,* parallel*-*group, multicentre, randomized study. The subjects will be 150 patients aged between 40 and 100 years of age with an at least 2-month history of a vascular venous ulcer assigned to ten primary care centres. For the treatment with autologous platelet rich plasma, all the following tasks will be performed in the primary care setting: blood collection, centrifugation, separation of platelet rich plasma, activation of coagulation adding calcium chloride and application of the PRP topically after gelification. The control group will receive standard moist wound care. The outcome variables to be measured at baseline, and at weeks 5 and 9 later include: reduction in the ulcer area, Chronic Venous Insufficiency Quality of Life Questionnaire score, and percentage of patients who require wound care only once a week.

**Discussion:**

The results of this study will be useful to improve the protocol for using platelet rich plasma in chronic vascular ulcers and to favour wider use of this treatment in primary care.

**Trial registration:**

Current Controlled Trials NCT02213952

## Background

The term ulcer is used to refer to spontaneous or traumatic lesions, typically in the lower extremities, that do not heal in a reasonable time, with an underlying aetiology that may related to systemic disease or local disorders. The healing process is complex and dynamic [1]. Once ulcers start to be treated, they eventually heal completely in most cases. However, due to some risk factors associated with the patient (comorbidities) or to the ulcer (infection), acute ulcers can become chronic [2].

Vascular ulcers represent a common severe health problem. Several studies report a prevalence of 1 to 2% for venous ulcers in the general population [3-6], and this type of ulcer represents 75 to 80% of all vascular ulcers. From these data, it can be estimated that in Spain there are between 250,000 and 300,000 people with venous ulcers, implying that 300,000 to 375,000 people have vascular ulcers.

In line with these figures, vascular ulcers represent a common disorder in daily medical practice at all levels but especially in primary care (PC). They have a significant impact at the individual, professional and social levels with a high cost in terms of human and material resources. However, it is still not well understood why venous ulcers develop, research efforts being ongoing to establish new theories on their pathogenesis [7]. Further, the current approach to their care does not always achieve adequate healing of these ulcers, and hence a range of alternative treatments is being tested [8,9].

Autologous platelet-rich plasma (PRP) is a product derived from blood that is increasingly widely used in clinical practice and, among other applications, it has become an alternative to the dressings used to date for the treatment of vascular ulcers. The curative properties of PRP rely on the fact that platelets are a physiological reservoir of growth factors, which have an active role in tissue regeneration. It is well known that platelets contain a great variety of growth factors, with healing functions [10].

On the other hand, despite evidence on the effectiveness of autologous PRP in venous ulcers, the effectiveness and feasibility of this treatment in the general population in primary care remain unclear. Most of studies have been limited to small groups of the population, in private clinics and hospitals [11]. The Salazar-Alvarez et al. prospective study, which is done in PC on 11 patients, concludes that PRP is a valuable and practical procedure that promotes the healing of chronic ulcers of the lower extremity [12]. However, it is necessary to conduct a well designed controlled clinical trial, examining the effect ofPRP in both ulcer healing and the patients’ quality of life. For these reasons, we propose a phase III clinical trial.

## Methods and design

### Hypothesis

After 2 months, treatment with PRP will lead to at least a 20% greater reduction in the ulcer area than observed in patients receiving standard care based on the current protocol in PC of moist wound care (MWC).

### Objectives

#### Primary objectives

To assess the efficacy in healing the ulcers attributable to autologous PRP by estimating the change in the ulcer area using serial photographs, at baseline and 5 and 9 weeks after starting the treatment, compared with that in the control group.

### Secondary objectives

To assess the safety of autologous PRP for the treatment of venous ulcers in patients with chronic venous insufficiency corresponding to C6 on the CEAP classification (C, clinical class, E, aetiology, A, anatomy and P, pathophysiology of the disease), describing changes in patient perceived pain, the percentage of ulcers with infection, and related perilesional changes, in both groups and comparing the results.

• To estimate the quality of life of patients in terms of the Chronic Venous Insufficiency Quality of Life Questionnaire (CIVIQ) score in both groups at baseline, and 5 and 9 weeks after starting the treatment.

### Study design

We will conduct a phase III open*-*label*,* parallel*-*group*,* multicentre*,* randomized study. We will analyse 150 patients between 40 and 100 years old who have venous vascular ulcers and are assigned to ten health centres of the Basque Health Service (Osakidetza) in the Ezkerraldea-Enkarterri, Barakaldo and Bilbao health region. Two groups will be formed: one intervention group, to be treated with autologous PRP and a control group, to be treated following the current recommendations for MWC.

Treatment with autologous PRP involves five steps: blood collection, centrifugation, separation of PRP, activation of the coagulation process using calcium chloride and placement of the PRP dressing, covering it with a secondary dressing.

Given that it is not feasible to use a placebo that could blind those involved to the use of the autologous PRP, the control group will receive conventional treatment of MWC, which is the usual care provided in our health service, and this will be carried out in accordance with the recommendations of Basque Health Service (Osakidetza).

### Study setting

The study is to be conducted in the PC health centres of, eligible patients being all those with venous vascular ulcers aged between 40 and 100 years of age under the care of Ezkerraldea-Enkarterri, Barakaldo and Bilbao health region, these centres and currently being treated with MWC in accordance with the recommendations of Basque Health Service (Osakidetza).

### Inclusion criteria

To be included, patients should meet all of the following criteria:Resident in Barakaldo or Bilbao seen in the treatment rooms of the PC health centres of the Ezkerraldea-Enkarterri and Bilbao health region of Osakidetza, for MWCAged between 40 and 100 years of age of either sexChronic venous insufficiency corresponding to C6 on the CEAP classificationVascular ulcer that does not respond to conventional treatment in 2 monthsNormal blood test results in terms of platelet and red blood cell counts and haematocritOne or two ulcer together whose area is equal or less than 20cm^2^Patients with a negative analytical on syphilis, Hepatitis B, Hepatitis Cand HIV I/IIAnkle Brachial Index ≥0.8 and ≤1.5Independent or with sufficient family support to travel to the health centreInformed consent form signed

### Exclusion criteria

Patients will be excluded if any of the following apply:Being pregnant or breastfeeding, or a woman of fertile age not using contraceptive methodsChronic use of immunosuppressants or antiretroviral drugsPatients with syphilis, Hepatitis B, Hepatitis Cand HIVClotting disordersChronic infectious diseasesTreatment with radiotherapy or chemotherapyHistory of cancerActive infection or fever at the beginning of the studyABI below 0.8 or above 1.5People who are taking a drug under clinical investigation or participated in any study under clinical investigation in the previous 30 days

### Reasons for withdrawal from the trial

Patients are free to withdraw from the trial at any time. If patients develop signs of infection with a visible exudate, they will be assessed by the research team, and it will be decided, together with the patient whether or not they should continue in the study, this event being recorded in the final report. In addition, they will be withdrawn if any of the following apply:Poor course of the ulcer with significant oedema, signs of regional infection, lymphangitis, cellulitis or excessive painWound care management by people other than those on the research teamInability or failure to attend scheduled appointmentsProblems with vascular accessInability to travel to the health centre by themselves or insufficient family support (coming to light after the start of the trial)Meeting any exclusion criteria during the course of the studyAny other problems that in the opinion of the research team justify treatment withdrawal.

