### Protocol

#### Control group

Patients in the control group will be treated as they had been prior to inclusion, that is, two to three times a week and in accordance with the health region recommendations, namely to maintain a moist healing environment. The wound care will consistently be provided by the same nurse, who will be responsible for making the appointments within the available timetable in the treatment room. The data will be registered in an Access database by the administrator. The treatment schedule for the control group is displayed in Tables 1 and 2.

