### Intervention group

Patients in the intervention group will receive wound care once a week with autologous PRP, based on the estimated mean lifespan of platelets (7–10 days). The treatment with autologous PRP will be performed in the assigned outpatient clinic, in the phlebotomy room, by qualified nurses ([name]).

As in the control group, the nurse will be responsible for making appointments for the next treatment and will collect data to be entered in an Access database by the administrator. The first treatment session of the study will be performed on day 8, and the data will be recorded in the patient medical record. From this point onwards, data will be collected every 7 days for 9 weeks. Treatment schedule for the PRP group is shown in Table 2.

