### Follow-up period

The follow-up period will last for 9 weeks, but all the adverse effects that appear within 30 days of stopping the treatment will be recorded.

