### Statistical analysis

The categorical variables will be presented as frequencies and percentages (for example, the percentage of patients requiring ≤1 weekly treatment) and continuous variables using measures of central tendency and dispersion (mean and standard deviation for normally distributed variables, and otherwise median and interquartile rank).

The analysis of the efficacy will be carried out on an intention-to-treat basis by comparing the percent reduction in ulcer area, observed in each of the groups after 5 and 9 weeks of treatment, with respect to baseline. Using the Mann–Whitney U non-parametric test, we will estimate the effect attributable to the intervention using the difference between the changes occurring in the two groups.

Subsequently, in order to adjust the comparisons for the baseline measurements, we will carry out covariance analysis models. As well as adjusting for baseline, we will adjust for the potential confounding or effect-modifying covariates. A p value <0.05 will be considered statistically significant.

All the analyses will be performed using SAS version 9.2 statistical software.

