### Limitations of the study

Taking into account that the treatment applied to both groups consists initially of a topical treatment, with significant differences in the appearance of the dressing to be applied, patients will be aware of their group allocation, as will the researchers, meaning that it is not feasible to double blind the study. To prevent the results of the research being influenced by observer bias, the progress of the ulcers will be assessed by someone independent of the research team, who will have exclusive access to photographs of the ulcers, with no type of identifying data related to the patient or their group.

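### As worded, the withdrawal rule can take randomised patients out of the study for reasons linked to ulcer area, which conflicts with the planned intention-to-treat comparison

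*Protocol article*

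**What the plan says.** The section *Reasons for withdrawal from the trial* in the Protocol article has two clinical routes out after randomisation.

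- **Local infection with visible exudate.** The research team assesses the patient, and then "it will be decided, together with the patient whether or not they should continue in the study". The trigger is stated; what should guide the decision is not.
- **A complicated poor course.** Withdrawal is mandatory if the ulcer does badly together with marked oedema, regional infection, lymphangitis, cellulitis or excessive pain. Slow healing alone is not on the list.

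The same mandatory list includes trouble with vascular access. It closes with a catch-all for other problems that "in the opinion of the research team justify treatment withdrawal". This is the only place in the section that refers to stopping treatment; the heading and the infection sentence refer to the trial or the study.

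Elsewhere, *Limitations of the study* says that "patients will be aware of their group allocation, as will the researchers". *Statistical analysis* says: "The analysis of the efficacy will be carried out on an intention-to-treat basis by comparing the percent reduction in ulcer area", at weeks 5 and 9 against baseline. *Sample size* allows for 30% withdrawal.

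**The concern.** An intention-to-treat comparison needs the outcome of every randomised patient as far as it can be obtained, whatever happens to the allocated treatment. Infection and a complicated course are plausibly associated with a smaller reduction in ulcer area. If these events end participation, and the week-5 or week-9 photograph is then not taken, the patients compared are a selection made partly on prognosis after randomisation. For infection, people who know the arm make that selection case by case.

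Removal also need not be equal between arms. "Treatment with autologous PRP involves five steps: blood collection, centrifugation, separation of PRP", and blood is drawn only for PRP, so the vascular access item can in practice remove only PRP patients. That item is not outcome-related in the text; it shows only that losses under this section may differ by arm.

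The masked reading of photographs by an independent assessor does not help, because nobody can read a photograph that was never taken. For the same reason, an analysis plan written later can choose how to treat missing areas but cannot recover them.

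**Working it through.** **1. What the wording supports**

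| Place in the Protocol article | What it points to |
|---|---|
| Withdrawal section, heading | leaving the trial |
| Withdrawal section, infection sentence | staying in or leaving the study |
| Withdrawal section, mandatory list | withdrawal, under that heading |
| Withdrawal section, last item | stopping treatment |
| *Statistical analysis* | outcomes of all patients as randomised |
| *Follow-up period* | nine weeks of follow-up, plus adverse effects for 30 days after treatment stops; silent on photographs after stopping |

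The heading, the infection sentence and the list under that heading point to leaving the study. One phrase points to treatment. The text is ambiguous, and the more natural reading is the one that conflicts with intention to treat.

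**2. The plan's own figures**

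*Sample size* gives 150 patients (75 per arm), a 15-point difference, α = 0.05, 80% power and 30% withdrawal. Then 150 × 0.30 = 45 expected withdrawals, and 75 × 0.70 = 52.5 patients left per arm. No standard deviation is stated, so 150 cannot be reproduced directly. Solving backwards (two-sided α assumed), SD = 15 / [(1.960 + 0.842) × √(2/n)] gives 27.3 for n = 52 and 27.6 for n = 53. This is circular. It shows only that 150 is compatible with counting withdrawn patients as lost, and it says nothing about why they withdraw. The point does not depend on it.

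**3. Possible size (illustration only)**

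The article gives no event rate, no healing deficit and no split of withdrawals by arm. All of the following are assumptions:

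- The arms are truly equal, and event-free patients have a mean area reduction of 50% in both. The 50 cancels in the difference.
- A share p of each arm has an infection or complicated-course event: 5%, 10% or 20%.
- Patients with an event have a mean reduction d points lower: 20 or 40.
- A share w of those patients leaves and is not analysed: 60% in one arm and 40% in the other. An extreme case uses 80% and 20%.

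Mean among patients still in an arm = 50 − d·p·(1 − w)/(1 − p·w).

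Worked case, p = 0.20 and d = 40:

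- w = 0.6: 50 − 40 × 0.20 × 0.4 / 0.88 = 46.36
- w = 0.4: 50 − 40 × 0.20 × 0.6 / 0.92 = 44.78
- False difference: 1.58 points

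| Split | d | p = 5% | p = 10% | p = 20% |
|---|---|---|---|---|
| 60/40 | 20 | 0.20 | 0.40 | 0.79 |
| 60/40 | 40 | 0.40 | 0.80 | 1.58 |
| 80/20 | 20 | 0.60 | 1.20 | 2.38 |
| 80/20 | 40 | 1.20 | 2.40 | 4.76 |

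The 15 points are read here as percentage points of area reduction. The 60/40 rows are then 0.20/15 = 1% to 1.58/15 = 11% of the target difference. The largest extreme value is 4.76/15 = 32%. With equal w the difference is 0. If the split reverses, so does the sign: the arm that loses more of its poor-course patients looks better.

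**The case against.** The strongest reply is that the text can be read consistently with intention to treat. The last list item begins by referring to other problems and ends with stopping treatment, which suggests that the items before it are also reasons to stop treatment. No sentence says that withdrawn patients are no longer photographed, and the article condenses a fuller protocol that may settle this. Stopping for cellulitis or severe pain, and sharing the decision about a local infection, is ordinary clinical practice. The figures above are wholly assumed and mostly small, and they are shifts in means, whereas the first test planned is Mann–Whitney.

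Much of this stands. The text is ambiguous, the clinical rules for stopping treatment are sound, and the figures do not carry over directly to the Mann–Whitney test. What does not stand is that this is mere missing detail. The article states a rule, places it under withdrawal from the trial, and lets continuation in the study itself be decided. Followed as written, it conflicts with the stated analysis.

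A reader might infer three stronger points that the document does not support:

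- **That photographs stop when treatment stops.** *Follow-up period* adds "but all the adverse effects that appear within 30 days of stopping the treatment will be recorded", which could look like a limit to safety data. The same sentence first sets a nine-week follow-up without tying it to treatment. It is silent on photographs after stopping and is not evidence either way.
- **That controls will be lost more often through missed visits.** Controls are seen "two to three times a week and in accordance with the health region recommendations", while "Patients in the intervention group will receive wound care once a week with autologous PRP". More visits give more chances to miss one, but that this leads to more removals is conjecture, and nothing here rests on it.
- **That the bias favours PRP.** Nothing in the article fixes which arm would lose more poor-course patients.

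**Conclusion.** The point holds as a conflict between a stated withdrawal rule and the stated intention-to-treat analysis, and it should be corrected. Confidence is medium, because the closing item of the list leaves room for a harmless reading. The direction and size of any bias are unknown. Under the assumed event rates, deficits and 60/40 split, the bias is about 0.2 to 1.6 points of mean area reduction. Larger values, up to 4.8, need an 80/20 split, a 20% event rate and a 40-point deficit all at once. Under the same assumptions, which include equal event rates in the two arms, it is zero if equal shares leave. It is also zero if all these patients are still photographed and analysed. The reason to act is less the expected size than that the data cannot be recovered once the photographs have been missed.

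**What to change.** In *Reasons for withdrawal from the trial*:

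1. Make infection, a complicated poor course and vascular access problems reasons to stop or change the allocated treatment, not reasons to leave the study. Clinical management stays with the treating team.
2. Record the reason for stopping, by arm.
3. Take the Day 36 and Day 64 photographs, already scheduled in Tables 1 and 2, for every randomised patient unless consent is withdrawn.
4. Analyse them in the randomised arm, as *Statistical analysis* already intends.

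**Cost.** Protocol wording and one field on the case report form. In both splits above, the number leaving is 75 × p × (w₁ + w₂) = 75 × p × 1.0, that is 3.75, 7.5 or 15 patients. At two photographs each, this means up to about 8 to 30 photographs after stopping. If all 45 withdrawals allowed for in *Sample size* were kept in follow-up, the ceiling is 45 × 2 = 90. The downside is these visits for patients who have stopped treatment, some of whom may find travel hard. No additional patients are needed.

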### Sample size

The estimated sample size is 150 patients, based on a previous meta-analysis by Martinez-Zapata et al. [13]. The patients will be randomly allocated to the intervention (treatment with PRP) or the control group (standard moist wound care), in a 1:1 ratio which involves 75 patient per group. The calculation is based on a clinically meaningful difference of at least 15 points between groups, for α = 0,05 and β = 20%, and considering 30% of withdrawal.

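### The withdrawal rule takes patients out of the trial for partly outcome-related and arm-dependent reasons and does not provide for their week 5 and 9 outcomes, which the promised intention-to-treat analysis needs

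*Protocol article*

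**What the plan says.** The list in the protocol article is headed "Reasons for withdrawal from the trial", and its wording is mandatory: "In addition, they will be withdrawn if any of the following apply". Three kinds of reason matter here.

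- **Related to the outcome:** "Poor course of the ulcer with significant oedema, signs of regional infection, lymphangitis, cellulitis" or excessive pain.
- **Related to the arm or to attendance:** problems with vascular access, failure to attend appointments, wound care by people outside the team, and inability to travel.
- **Open-ended:** any other problem that the research team thinks sufficient. The Limitations section says that researchers know the allocation.

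The last item speaks of withdrawing treatment, whereas the heading speaks of the trial.

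Under Statistical analysis: "The analysis of the efficacy will be carried out on an intention-to-treat basis", comparing percent reduction in ulcer area at weeks 5 and 9. Under Sample size, 150 patients (75 per group) are planned for a 15-point difference, "considering 30% of withdrawal". The Follow-up period section mentions only adverse effects as being recorded after treatment stops.

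**The concern.** An intention-to-treat comparison needs the outcome of every randomised patient, or as near to that as can be achieved, whether or not treatment continued. A rule that ends trial participation when the ulcer does badly tends to remove patients with less area reduction. If such losses differ between the arms, the patients left are no longer the groups that randomisation made comparable.

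The masked reading of photographs described under Limitations does not protect against this, because the selection happens before the photograph is taken. Nor can an analysis plan repair it. Such a plan can choose a method for missing data, but it cannot restore photographs that were never taken.

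**Working it through.** **1. The passages side by side**

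- *Outcome.* The primary variable is percent reduction in ulcer area. A poor course with oedema, infection or pain is a complication criterion. It overlaps with poor area reduction but is not identical to it.
- *Arm.* "Treatment with autologous PRP involves five steps: blood collection, centrifugation, separation of PRP" (Study design), and "Patients in the intervention group will receive wound care once a week with autologous PRP" (Intervention group). Table 2 shows eight such sessions, Day 8 to Day 57. Moist wound care needs no blood draw, so withdrawal for vascular access falls in practice on the PRP arm.
- *Attendance.* Controls come "two to three times a week and in accordance with the health region recommendations", and PRP patients once a week. The schedules differ, but the article does not show which arm would miss more.
- *After withdrawal.* No section provides for a photograph or CIVIQ.

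**2. The planned loss**

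0.30 × 75 = 22.5 per arm, or 45 of 150. About 52 per arm remain.

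**3. The sample size**

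No SD is stated, so 150 cannot be reproduced from the article's own inputs. Solving backwards, with two-sided alpha 0.05 (sidedness is my assumption), 80% power and 52 analysed per arm:

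SD = 15 / [(1.960 + 0.842) × √(2/52)] = 27.3 points.

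Check: n = 2 × 2.802² × 27.3² / 15² = 52, and 52 / 0.70 = 74.3, rounded up to 75 per arm, 150 in total. The figure of 150 therefore fits a calculation in which withdrawn patients contribute no outcome. The SD remains an inference.

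**4. Size of the possible bias**

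Assume a normal outcome with SD 27.3, and a correlation ρ between clinical course and final area reduction. Losing the fraction w with the worst course raises the mean of those left by

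ρ × SD × φ(z_w) / (1 − w),

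where z_w is the normal quantile at w. The factor φ(z_w)/(1 − w) is 0.274 at w = 0.15, 0.350 at w = 0.20 and 0.497 at w = 0.30.

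False difference when the true difference is 0:

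| Poor-course loss in the two arms | ρ = 0.5 | ρ = 0.7 | ρ = 1.0 |
|---|---|---|---|
| 30% and 30% | 0 | 0 | 0 |
| 30% and 15% | 3.0 | 4.3 | 6.1 |
| 30% and 0% | 6.8 | 9.5 | 13.6 |

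For example, at ρ = 1.0 the second row is (0.497 − 0.274) × 27.3 = 6.1. The false difference favours whichever arm loses more patients with a poor course.

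When the true difference is 15 and one common poor-course threshold removes 30% of controls, the PRP arm loses 21%, 18% or 14% (ρ = 0.5, 0.7, 1.0). The difference among those left is then about 13.2, 11.7 or 8.6 points, so the effect is understated.

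**5. What continued follow-up would give**

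With 75 per arm analysed and SD 27.3, power for 15 points is Φ(15 / [27.3 × √(2/75)] − 1.960) = 92%, against 80% with 52. This is before any dilution of the effect by stopped treatment.

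**The case against.** The strongest reply is that the end of outcome collection is inferred. The last list item refers to treatment, the analysis is declared intention-to-treat, and a journal article may leave follow-up detail to the full protocol. That stands as a limit. But the heading, the mandatory wording, the post-treatment recording of adverse effects alone and the 30% allowance all point the same way, and a site following this text would have no reason to photograph a withdrawn patient.

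A reader might also be tempted by four stronger readings, which the document does not support:

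- *The analysis is a completer analysis.* The handling of missing outcomes may be in an analysis plan that is not shown, and patients withdrawn after the week 5 assessment already have that value.
- *Treatment failures are deleted.* An ulcer that merely fails to shrink does not meet the criterion, which requires complications or excessive pain.
- *The bias comes close to the whole target.* If one arm loses exactly its worst 20% or 30% on the final outcome and the other loses the same share at random, the false difference is 0.350 × 27.3 = 9.6 or 0.497 × 27.3 = 13.6 points. These are extreme cases: they need ρ = 1 and a contrast between arms that nothing in the article suggests, since the poor-course rule applies to both. At ρ = 0.5 they halve to 4.8 and 6.8.
- *Missed appointments fall mainly on controls because they have more visits.* The article gives no rate of missed visits and does not say that one missed visit leads to withdrawal. Controls keep their previous schedule, whereas PRP patients go to an assigned outpatient clinic. The direction is unknown.

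**Conclusion.** The concern holds in this form: the withdrawal rule conflicts with the promised intention-to-treat analysis, because it mandates leaving the trial for reasons that are partly related to the outcome and, for vascular access, to the arm, without providing for later outcome assessment. The open-ended criterion, applied by a team that knows the allocation, adds to this.

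The possible bias ranges from near zero, with equal loss and no true effect, through about 3 to 6 points (30% against 15% poor-course loss), to about 7 to 14 points (30% against 0%), beside a 15-point target. These figures rest on a back-solved SD, a normal outcome and assumed correlations and loss rates. They show what the rule permits and do not predict what will happen. The direction cannot be fixed from the article: under a common threshold with a true benefit the error is conservative, while greater poor-course loss in the PRP arm would flatter PRP.

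**What to change.** - Leave the clinical reasons as they are, but restate the list as reasons for stopping study treatment.
- State that every randomised patient still has the ulcer photograph and CIVIQ at weeks 5 and 9 unless consent to follow-up is withdrawn, and is analysed in the allocated group.
- Record missed appointments and wound care by outside staff as adherence data, and not as reasons to end follow-up.
- Optionally, add a sensitivity analysis that gives the worst rank in the Mann–Whitney comparison to patients who stop for a poor ulcer course and have no photograph.

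The cost is a change of wording and up to two extra assessments for each patient who stops treatment. Some patients who cannot travel will still miss them, and patients remain free to leave, so 75 analysable per arm and the 92% power are ceilings.
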